### Study design

We will conduct a RCT using a 2×2 factorial design (physician communication x social observational learning, both with the levels yes/no) with repeated measurements. Patient visits and the administration of questionnaires will be done at various time points: preoperatively, 4 days before surgery (baseline), postoperatively during the hospital stay on day 1 and day 4 (discharge day), as well as at 4 weeks, 3 months, 6 months and 12 months after surgery. In addition to the intervention, patients will be provided with a pain diary and questionnaires to fill out throughout the postoperative period. The follow-up assessments are scheduled at 4 weeks, 3 months, 6 months and 12 months after THA.

The effects of both interventions will be tested on subjective and objective pain measures, including visceral and somatic pain reports (cf. in detail 3).

### Patients

We will include 200 patients undergoing THA at the University Medical Center Hamburg-Eppendorf, UKE, Department of Trauma and Orthopaedic Surgery, performed at a UKE external location (Helios ENDO-Clinic Hamburg).

Participants will be eligible or ineligible based on the following inclusion and exclusion criteria:

#### Inclusion criteria

Age ≥18 years.THA due to OA (diagnosed according to the S3 guidelines of the German Society for Orthopaedics and Trauma Surgery (DGOU)).Fluent proficiency in the written and spoken German language.

#### Exclusion criteria

Presence of one or more malignancies or similar diseases that require treatment.Severe acute or chronic mental health condition (e.g., schizophrenia).Severe cognitive impairments or dementia.Substance abuse (including harmful use of opioids, ICD-10 F11.1, or opioid dependence syndrome, ICD-10 F11.2); note: patients will not be excluded for temporary opioid intake prescribed to bridge the time interval until THA.Secondary THA (revision or prior contralateral THA)Pregnancy or breastfeeding.

#### Admission and Enrolment of the patients

The preoperative consultation is performed by the treating physician at the Helios ENDO-Clinic in Hamburg, a leading high-volume arthroplasty centre with high expertise. Based on the patient’s symptoms, imaging and established THA guidelines, surgery will be recommended as the appropriate treatment. Following the diagnosis of OA and the planning of primary THA, the practitioner will screen the patient for study eligibility using a checklist. Patient meeting the inclusion criteria will receive detailed information about the study. If they consent to participate, they will be enrolled and subsequently randomised to their respective intervention groups. All participants will receive oral and written information and must provide written informed consent before enrolment. A sample of the patient information and consent form is available in the online supplemental materials.

### Intervention and study groups

The intervention is delivered at two time points: 4 days before surgery (during the preoperative consultation) and on the first postoperative day. These timings are chosen to optimally shape and reinforce patient expectations.

#### Augmented communication-based expectation manipulation (aDOC)

The intervention consists of a structured physician-patient conversation developed for this study, drawing on findings from placebo research and expectation-based interventions in pain and surgical outcomes. It targets both the cognitive dimension, by providing clear and understandable medical information about the procedure, postoperative course and expected recovery, and the emotional dimension, by expressing empathy, warmth, and reassurance.

Randomisation takes place at the baseline visit, approximately 4 days before surgery. On the same day, participants receive their assigned intervention. The physician conversation is during the preoperative visit and focuses on establishing realistic yet positive expectations, addressing potential patients concerns and supporting the patient’s sense of control. The postoperative session, on the first day after surgery, reinforces these expectations, encourages adaptive coping strategies and strengthens the therapeutic relationship.

The intervention is conceptually based on evidence demonstrating that the doctor-patient interaction itself can influence clinical outcomes. Previous studies have shown that positive expectations can reduce symptom intensity and analgesic use, and that the combination of physician warmth and competence produces the strongest effects on patient experience and symptom relief.^8 10 30 31^ The standardised approach ensures consistency while allowing flexibility to respond to individual patient needs.

#### Video-based treatment expectation manipulation

Patients in two of the four groups will watch a 10-min. video containing standardised study information. The video provides insight into another patient’s experience with hip-related pain, functional impairments and the subsequent surgery.

In the first part, the clinic director welcomes the viewers and explains the course of their hospital stay. The next section features a patient demonstrating how hip pain and functional limitations affect various everyday activities. This is followed by a depiction of the same activities after the hip arthroplasty, but this time without pain or impairments, illustrating the potential impact of treatment. While the video content is identical, we prepared two different videos to account for potential gender effects, featuring both a male and a female patient. The patients featured in the video are approximately 60 years old, aligning with the target study population.^32^ Participants will be randomly assigned to watch one of the two versions. Only participants of groups 1 and 3 will be shown the video intervention (figure 1). The video is presented twice: first during the preoperative baseline visit and again on the first postoperative day to reinforce what they have learnt and to support expectation maintenance during early recovery.

**Figure 1 F1:**
[figure not shown]
Study design. Schematic illustration of the study design for evaluating the impact of preoperative education on postoperative outcomes in patients undergoing total hip arthroplasty (n=200). Patients are randomised (R) into one of four groups: combined doctor consultation and video intervention (aDOC+VIDEO), doctor consultation only (aDOC), video only (VIDEO) or treatment as usual (TAU). All groups undergo surgery followed by standardised postoperative hospital care. Assessments are conducted at preoperative baseline, daily during the postoperative hospital phase (including pain diary and medication use) and at follow-up visits at 3 months (3M) and 6 months (6M) post-surgery.

#### Study groups

After meeting the eligibility criteria and providing written informed consent, participants will be randomly assigned to one of the four study groups.

##### Group 1: aDOC + Video

Participants receive the augmented physician-patient communication during the preoperative and postoperative consultation, in addition to watching a 10-min video depicting a patient who has undergone THA.

##### Group 2: aDOC

Participants receive the augmented physician-patient communication during the preoperative and postoperative consultation, but do not watch the video.

##### Group 3: Video

Participants receive standard clinical consultation but watch the same video as Group 1.

##### Group 4: Treatment as Usual

Participants receive the standard preoperative consultation provided by the clinic, without any additional interventions such as the enhanced conversation or video.

### Blinding and randomisation

The study researcher responsible for analysing the primary outcomes will remain blinded to group allocation by working with a concealed group variable (group variable with hidden label). Since the intervention involves direct delivery by the study physician, the physician must be aware of group assignment to conduct the informed consent process using augmented communication where applicable. To minimise researcher bias, only trained study physicians deliver the augmented consultations (aDOC), while standard consultations (TAU) are provided by clinicians who are not involved in the intervention. Study staff administer the video separately after the physician’s visit, ensuring that consulting physicians remain unaware of whether a participant has received it. This design intentionally introduces a potential experimenter effect, allowing for the investigation of the impact of enhanced physician-patient interaction as part of the intervention itself (‘effects of augmented communication’). Blinding of the study researcher, who is unaware of the group allocation, is designed to minimise this risk as much as possible.

Participants will be randomly assigned to one of the four study groups using a block randomisation method to ensure balanced group sizes throughout the recruitment period. The block size will be kept constant at 20 and will not be disclosed to the physicians involved in recruitment. Allocation concealment will be achieved by using sealed, opaque and sequentially numbered envelopes. Each patient will draw one envelope on inclusion, thereby determining their group assignment by chance. This procedure ensures both randomisation integrity and transparency while minimising selection bias.

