### Methods to optimise treatment expectation: observational learning and augmented communication

Treatment expectations are shaped through various mechanisms, including conditioning based on prior experiences.^22^,^24^ Moreover, research suggests that these expectations can be influenced by observing others who have experienced positive treatment outcomes.^1025^,^27^ An additional mechanism relates to communication. Patients often benefit significantly from direct interaction with others, especially healthcare providers. However, such opportunities, for example, augmented communication, are often limited in clinical settings.^28^ While most of the existing evidence on the impact of expectations stems from experimental studies with healthy volunteers, it is important to recognise that the desire for pain relief may differ significantly between healthy individuals and patients undergoing surgery.^24^ In a clinical study, Stuhlreyer *et al*^29^ demonstrated that augmented physician communication aimed at improving treatment expectations significantly reduced postoperative pain after total knee arthroplasty. Building on these findings, it is obvious to address both methods to optimise patients’ treatment expectation and to investigate whether (1.) prerecorded videos of patients who have successfully benefited from the treatment, (2.) physician communication reflecting warmth and competence and (3.) a combination of both can maximise patients’ positive treatment expectations and enhance treatment outcomes.

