### Statistical analysis

Differences in clinical outcomes between and within groups will be assessed using ANOVA for the various outcome measures. Most outcomes in this study (e.g., pain intensity, functional scores and self-efficacy and inflammatory markers) are continuous and will be analysed as such. A small number of secondary outcomes, however, are categorical (e.g.,analgesic use) and will be analysed using appropriate methods, such as chi-square tests or logistic regression, depending on the data structure. Data analysis will follow the intention-to-treat principle and will be conducted by a researcher blinded to group assignments. If significant main and interaction effects are identified, post hoc analyses (e.g., Least Significant Difference (LSD)) will be performed. The statistical analyses will be carried out using IBM SPSS Statistics software version 27.0 (IBM Corp), with results presented as means and 95% confidence intervals unless stated otherwise. If required, adjustments for deviations from sphericity will be made using Greenhouse-Geisser or Huynh-Feldt corrections for the F-test df. A two-sided p-value of <0.05 will be considered the threshold for statistical significance in all analyses.

Missing data will be handled using multiple imputation, provided that the necessary assumptions are fulfilled. Participants with extensive missing data (e.g., no primary outcome data at any timepoint) will be excluded from the respective analysis. Alongside the intention-to-treat (ITT) approach, we will conduct a per-protocol sensitivity analysis, excluding participants who did not receive the full assigned intervention. This enables us to assess the robustness of results at different levels of complexity.

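### The aDOC contrast compares two separate sets of doctors, so it estimates a delivered package, and its confidence interval is too narrow if outcomes cluster by physician

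*Protocol article*

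**What the plan says.** Study design sets out the factorial: "We will conduct a RCT using a 2×2 factorial design (physician communication x social observational learning, both with the levels yes/no) with repeated measurements". Blinding and randomisation fixes who delivers each level of the communication factor: "only trained study physicians deliver the augmented consultations (aDOC), while standard consultations (TAU) are provided by clinicians who are not involved in the intervention". The Video-only group falls on the no-aDOC side as well: "Participants receive standard clinical consultation but watch the same video as Group 1". Groups 1 and 2 therefore see study physicians, and groups 3 and 4 see other clinicians. Patients are randomised individually, in blocks of 20.

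The same section acknowledges the consequence: "This design intentionally introduces a potential experimenter effect, allowing for the investigation of the impact of enhanced physician-patient interaction as part of the intervention itself". The safeguard it offers is a blinded researcher.

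On analysis, Statistical analysis states: "Differences in clinical outcomes between and within groups will be assessed using ANOVA for the various outcome measures". Results come "with results presented as means and 95% confidence intervals unless stated otherwise", and "A two-sided p-value of <0.05 will be considered the threshold for statistical significance in all analyses". The abstract specifies repeated measures ANOVA. Neither place names a physician term. Sample size calculation gives n=164 for f=0.15, α=0.05 and power 0.90, raised to 200, or 50 per group.

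**The concern.** Two separate things follow from this allocation of doctors.

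The first is what the contrast means. No doctor gives both kinds of consultation, so any average difference between the two sets of doctors is part of the estimated aDOC effect. Randomising patients cannot separate it from the communication. The study aims, however, are phrased in terms of physician communication, and the introduction asks about "physician communication reflecting warmth and competence".

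The second is precision. Patients of one doctor share that doctor's manner. The article itself gives reason to expect that this matters: it bases aDOC on evidence that the doctor–patient interaction influences outcomes, leaves room to adapt to the individual patient, and measures CARE and warmth/competence. If outcomes are correlated within physician, the effective sample for the aDOC contrast is smaller than the patient count, and an ANOVA on independent patients understates the standard error.

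The conclusion on one of the trial's two factors is at stake: how it is worded and how much certainty is attached to it.

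**Working it through.** **The plan's own figure.** The article does not give the number of measurements or the correlation behind n=164. The within–between interaction form reproduces it with 4 groups, 2 measurements and correlation 0.5 (the last two are assumptions):

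- λ = f²·N·m/(1−ρ) = 0.0225 × 164 × 2 / 0.5 = 14.76
- df = 3 and 160, power 0.905. At N=160 the power is 0.897, so 164 is the smallest multiple of 4 that reaches 0.90.

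Other settings also give 164 (7 measurements with ρ=0; or a between-group test with 4 measurements and ρ=0). None of these formulas contains a design effect for physicians.

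**Inputs for the clustering check.** From the article: 200 patients, 50 per group, so 100 per aDOC level; two-sided 0.05. Assumed, because not stated: J physicians per level with equal caseloads, and ICC between 0 and 0.05. The ICC is that of the quantity compared, for example the baseline-adjusted post-baseline outcome.

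**Formulas.**

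- Design effect: DE = 1 + (100/J − 1) × ICC
- Factor by which the planned SE is too small: √DE
- True two-sided error of the nominal 5% test: 2 × [1 − Φ(1.96/√DE)]
- Width of an interval on 2J−2 df relative to the planned one: √DE × t(2J−2) / t(196), with t(196) = 1.972

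Example, J=4 and ICC=0.02: DE = 1 + 24 × 0.02 = 1.48; √DE = 1.217; error = 2 × [1 − Φ(1.611)] = 10.7%; width ratio = 1.217 × 2.447 / 1.972 = 1.51.

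| J per level | ICC | DE | SE factor | True error | Width ratio |
|---|---|---|---|---|---|
| any | 0 | 1.00 | 1.00 | 5.0% | – |
| 10 | 0.01 | 1.09 | 1.04 | 6.0% | 1.11 |
| 10 | 0.02 | 1.18 | 1.09 | 7.1% | 1.16 |
| 10 | 0.05 | 1.45 | 1.20 | 10.4% | 1.28 |
| 4 | 0.01 | 1.24 | 1.11 | 7.8% | 1.38 |
| 4 | 0.02 | 1.48 | 1.22 | 10.7% | 1.51 |
| 4 | 0.05 | 2.20 | 1.48 | 18.6% | 1.84 |
| 2 | 0.01 | 1.49 | 1.22 | 10.8% | 2.66 |
| 2 | 0.02 | 1.98 | 1.41 | 16.4% | 3.07 |
| 2 | 0.05 | 3.45 | 1.86 | 29.1% | 4.05 |

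Replacing 1.96 by 1.972 lowers the error figures by at most 0.3 percentage points (10.1%, 18.4% and 28.8% at ICC 0.05).

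**Which contrasts are touched.** Every contrast that crosses the aDOC levels is touched, including post hoc comparisons such as aDOC against TAU. Measuring change from baseline does not help, because T-4a precedes the consultation: the doctor's influence falls on later values and so on the group × time term. The Video main effect compares patients within the same set of doctors, and the aDOC × Video interaction compares two such within-set differences. Study staff show the video after the physician's visit. Average doctor differences therefore largely cancel in both.

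**The case against.** The strongest reply is that the article discloses this. It gives a reason for separate physicians (limiting researcher bias), accepts the experimenter effect as part of the intervention, and treats warmth and competence as its active ingredients. On that reading, warmer doctors in the aDOC arms are largely the treatment itself. This stands as a defence of a package estimand. It does not support a conclusion about communication as such. Nor does it deal with precision: chance differences between a few doctors remain in the package contrast, and a blinded analyst removes neither problem.

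A second reply is that a condensed article may leave a physician term to the full analysis plan. That is fair, and the mere absence of such a term is not the point here. The point rests on what the article fixes: who delivers which consultation, and ANOVA as the named method. A later plan could add the term, but it could not undo the allocation of doctors.

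A third reply is that the inflation is conditional. That stands in full. A reader might infer that the aDOC interval is certainly too narrow and the error rate certainly above 5%. The article does not support this: it gives no physician count and no ICC, with ICC = 0 there is no inflation, and with 10 doctors per level the excess is modest.

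Finally, a physician model has its own problems. It does not remove the aliasing, it can be very imprecise with few doctors, and physician ID reveals the aDOC level to the blinded analyst. All of this is right, and it is why the clustered model belongs beside the ANOVA and not in its place.

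**Conclusion.** The concern holds in conditional form. It is certain from the text that the aDOC main effect and the aDOC × time contrast estimate a package: aDOC by trained study physicians against standard consultation by clinic physicians. It is conditional on a physician ICC above 0 that the planned interval is too narrow. Over the ICC range 0 to 0.05, with equal caseloads, the true error goes from 5% up to about 10% (10 physicians per level), 18–19% (4) or 29% (2). The article does not show where in this range the trial lies.

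A reader might also infer that both factors, or the additive-versus-synergistic question, are compromised. They are not: the Video main effect and the aDOC × Video interaction are little affected. This is a cheap improvement that changes how the aDOC result can be stated; it does not invalidate the trial.

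**What to change.** 1. Record the consulting physician's ID at the preoperative consultation (T-4) and on the first postoperative day (T1), in coded form. Start while recruitment runs, as IDs may be hard to recover later.
2. Report the number of physicians, and of patients per physician, in each aDOC level.
3. Keep the planned ANOVA. Beside it, for every aDOC contrast, report a sensitivity analysis with a physician random effect nested in aDOC level and small-sample degrees of freedom (Satterthwaite or Kenward–Roger). Apply it to post-baseline, baseline-adjusted outcomes, or include a physician × time term; a plain intercept across all visits could miss an effect that begins only after the consultation.
4. If an arm has only one or two physicians, state that between-physician variance cannot be reliably estimated.
5. Run this model after the blinded primary analysis, because the ID reveals the aDOC level.
6. Word the aDOC conclusion as the package effect. The random effect widens the interval but does not separate doctor from communication, so this wording is needed whatever the model shows.

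Cost: one variable, one additional model and a sentence of interpretation. The downside is a wider aDOC interval in the sensitivity analysis: over ICC 0.01 to 0.05, 1.11 to 1.28 times as wide with 10 physicians per level, 1.38 to 1.84 times with 4, and 2.66 to 4.05 times with 2.

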ASES-D, Arthritis Self-Efficacy Scale German version; Behandlungserfolg PR-OP, Perceived Treatment Success Pre-/Post-Op; CARE, Consultation and Relational Empathy Measure; CRP, C-reactive Protein; DN4 / DN2, Douleur Neuropathique 4 / Douleur Neuropathique 2; ESR, Erythrocyte Sedimentation Rate; FSS, Fatigue Severity Scale; GCPS, Graded Chronic Pain Scale; GEEE-Effekt, Göttingen Questionnaire on Experience and Evaluation of Health Care Effect scale; GEEE-Erwartung, Göttingen Questionnaire on Experience and Evaluation of Health Care Expectation scale; Harris Hip Score, Harris Hip Score; IL-6, Interleukin-6; NRS, Numeric Rating Scale; PDI, Pain Disability Index; PSS, Perceived Stress Scale; QoR-15, Quality of Recovery-15; SBI (PHI), Surgical Behavior Inventory (Pain Health Inventory); SETS, Stanford Expectations of Treatment Scale; SSAS, Somatosensory Amplification Scale; STADI Trait / State, State-Trait Anxiety-Depression Inventory; T1, 1 day postoperative; T2, day of discharge; T3, 1-month follow-up; T4, 3-month follow-up; T5, 6-month follow-up; T-4b, 4 days preoperative, after the intervention; Timepoints: T-4a, 4 days preoperative, before the intervention; Wärme u. Kompetenz, Warmth and Competence Scale.

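### As written, the physician knows the four-arm assignment yet is said to be unaware of the video, and nothing places the T-4a ratings before the allocation envelope

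*Protocol article*

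**What the plan says.** All but the last two items below come from the section Blinding and randomisation of the protocol article.

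- **Allocation.** "Participants will be randomly assigned to one of the four study groups using a block randomisation method". The device is a sealed, numbered envelope: "Each patient will draw one envelope on inclusion, thereby determining their group assignment by chance".
- **What the physician knows.** "the physician must be aware of group assignment to conduct the informed consent process using augmented communication where applicable".
- **What the physician does not know.** Staff show the video separately once the physician's visit is over, "ensuring that consulting physicians remain unaware of whether a participant has received it".
- **Order of events.** Under Admission and Enrolment of the patients: "If they consent to participate, they will be enrolled and subsequently randomised to their respective intervention groups". Under the aDOC heading: "Randomisation takes place at the baseline visit, approximately 4 days before surgery", with the intervention on the same day. The aDOC physician has a second session on postoperative day 1. The video section puts one showing at the baseline visit and a second on postoperative day 1.
- **Definition of baseline.** The legend of Table 1 gives "T-4a, 4 days preoperative, before the intervention". T-4b is the rating after the intervention on the same day.

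**The concern.** Two separate things are at stake.

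The first is the factorial question. The article asks whether the two interventions simply add up or reinforce each other. That needs the same aDOC conversation in the aDOC and aDOC+Video arms. The conversation is standardised but leaves room to respond to the individual patient, so a physician who knows that the video is coming, or has been seen, could adapt it. Any such change would be counted as part of the interaction.

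The second is the baseline. At T-4a the patients rate themselves on the PHI (part of the primary pain assessment), SETS, GEEE expectation, ASES-D and STADI. In a trial about expectations, learning that one will or will not receive extra preparation could itself move these ratings. If the arm is known by then, T-4a is no longer a pre-randomisation baseline. The first key question, on preoperative expectations, relies most directly on the change from T-4a to T-4b. The Abstract also describes the primary analysis as a comparison of changes in pain intensity.

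**Working it through.** The plan gives no figure on this point to reproduce, and the sample-size calculation does not enter. The check is a comparison of statements, plus some simple algebra.

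**1. What the allocation result carries.** There are four groups of 50: aDOC+Video, aDOC, Video and TAU. Of the 50 + 50 = 100 patients with aDOC, 50 are to see the video.

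- A physician told only that the patient has aDOC: probability of video = 50/100 = 0.5, so no information.
- A physician told which of the four groups the patient is in: the video status is certain.

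Blinding to the video therefore depends entirely on which of these two the physician receives.

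**2. The two statements side by side.** The section uses *group assignment* for what the physician must know and again for what the single envelope determines. The envelope assigns one of four groups. Read consistently, the physician is in the second case above and knows the video status. The assurance that physicians stay unaware needs the first case. No step that passes on only the aDOC factor is described.

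**3. The stated safeguard against the schedule.** The only mechanism offered is that the video follows the physician's visit.

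| Time | Physician session (aDOC arms) | Has the patient already seen the video? |
|---|---|---|
| Baseline visit, about 4 days before surgery | Preoperative conversation | No, if the video follows |
| Postoperative day 1 | Second conversation | Yes in aDOC+Video, from the baseline visit |

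The ordering can work at the baseline visit. It cannot work on day 1, because a patient who knows what was shown at baseline may mention it, whoever opened the envelope.

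**4. Where T-4a sits.** The article fixes three orderings:

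- consent, then enrolment, then randomisation;
- the envelope drawn on inclusion;
- T-4a before the intervention.

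Randomisation and intervention share one day. The sequence consent, envelope, T-4a, intervention, T-4b satisfies all three, and so does consent, T-4a, envelope, intervention, T-4b. The definition does not rule out the first.

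**5. What the first sequence would do.** Let δ be the mean shift in a T-4a rating, between two arms, caused by knowing the arm. Let θ be the full between-arm difference at T-4b. Randomisation makes the arms equal in expectation before disclosure, so the expected difference in change is

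(T-4b difference) − (T-4a difference) = θ − δ.

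The change comparison is off by δ. It understates the effect if δ has the same sign as θ and overstates it if the sign is opposite. The same holds for change from T-4a to any later visit. For the interaction contrast, with δ now the shift in each cell, the error is −(δ for aDOC+Video − δ for aDOC − δ for Video + δ for TAU). This is zero if the shifts happen to be additive. Comparisons of arms at a postoperative visit that do not use T-4a are unaffected. The documents contain nothing from which δ could be estimated.

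**The case against.** The strongest reply is that these are matters of loose wording and condensed reporting. The physician's knowledge is tied to a purpose, delivering augmented communication where it applies, and for that only the aDOC factor is needed. Roles are separated: trained study physicians give aDOC, other clinicians give the standard consultation, and staff show the video. The patient draws the envelope, but the article does not say who opens it, what the insert shows or who sees it. If staff open it and pass on only aDOC status, the preoperative blinding works. The order of forms within one visit is detail that an article may leave to the full protocol. The section on patient involvement also mentions a condition with partial disclosure, so patients may learn less from the envelope than a four-arm label suggests. Finally, nothing shows that a structured conversation would be altered for video patients.

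Much of this stands. A reader might infer that the envelope does reveal the video allocation to physicians, or that T-4a ratings are in fact given after allocation. The text supports neither as fact; it only fails to exclude them.

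Three things remain. The wording on what the physician knows still conflicts with the assurance about the video. The day-1 session is not protected under any handling of the envelope. And T-4a is tied to the intervention when, for a baseline, the event that matters is disclosure of the allocation. That is a definition the article states, so it is more than an omitted detail.

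**Conclusion.** The point holds as an internal contradiction and a loosely fixed timepoint. The article both gives the physician the four-arm assignment and declares the physician unaware of the video. The ordering it relies on cannot secure that on postoperative day 1. Its definition of T-4a permits subjective baseline ratings after the arm is known.

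No size can be put on the consequence. A reader might be tempted to assume a shift in baseline ratings and compare it with the planned effect of f = 0.15. The documents do not support this. They give no value for such a shift and state no baseline covariate. The f refers to an interaction in a repeated-measures ANOVA, and the article states neither the number of measurements nor their correlation, so f cannot be turned into a standardised mean difference by the simple two-group rule.

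The conclusion on T-4a is conditional: bias arises only if patients know their arm when they complete the ratings, and only in comparisons that use T-4a. The conclusion on the interaction is conditional on a physician who knows of the video changing the conversation. The correction is still worth making, because it protects the first and third key questions at almost no cost.

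**What to change.** 1. **Baseline.** State that all T-4a measures are completed before the envelope is opened, and define T-4a in the Table 1 legend as before disclosure of the allocation as well as before the intervention.
2. **Disclosure to physicians.** State who opens the envelope, and that physicians are told only aDOC yes or no. One way is an outer part showing the aDOC factor and a sealed inner insert with video yes or no, opened by the staff member who shows the video once the physician has left. In the sentence on what the physician must know, replace *group assignment* with *aDOC assignment*.
3. **Blinding claim.** Limit the statement that physicians are unaware of the video to the preoperative consultation, or drop it for the day-1 session. The two-part envelope does not protect that session.

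The cost is a changed envelope insert, a line on the order of the baseline visit and a slightly weaker blinding statement. No extra visits or staff are needed. If the full protocol already fixes these steps, only the article's wording has to be aligned with it.
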